# Effect of the Nutraceutical Micodigest 2.0 on the Complication Rate of Colorectal Cancer Surgery With Curative Intent: Protocol for a Placebo-Controlled Double-blind Randomized Clinical Trial

**DOI:** 10.2196/34292

**Published:** 2022-05-16

**Keywords:** colorectal cancer, surgery complications, gut microbiota, inflammatory pattern, nutritional status, nutraceutical, postsurgery, colorectal, cancer, colon

## Abstract

**Background:**

Most colorectal cancer patients diagnosed are candidates for surgical resection with curative intent, although colorectal surgery is associated with some complications that could be life-threatening. Antibiotic prophylaxis is commonly used for the prevention of infectious postoperative complications. However, this intervention can change the composition of intestinal microbiota and promote adverse inflammatory outcomes in colorectal cancer patients. The combination of different fungal extracts could be beneficial because of their role in gut microbiota modulation and their anti-inflammatory activity.

**Objective:**

Based on this hypothesis, we have designed a double-bind, randomized clinical trial to evaluate the effect of the nutraceutical fungal extract Micodigest 2.0 on complications of surgery for colorectal cancer resection.

**Methods:**

Colorectal cancer candidates for surgery will be considered for inclusion in the study. After evaluation by the multidisciplinary tumor board, patients who meet selection criteria will be screened, stratified according to tumor location, and randomly allocated to be treated with Micodigest 2.0 or placebo. Treatment will be continued until admission for surgery (4-6 weeks). Participants will undergo a medical and clinical evaluation including baseline and preadmission quality of life, microbiome composition, inflammatory and nutritional status, adverse events, and adherence assessments. The main end point of the study is the surgery complication rate. We will evaluate complications using the Clavien-Dindo classification. It will be necessary to recruit 144 patients to find a relevant clinical difference. We will also evaluate the effect of the nutraceutical on microbiome composition, inflammatory response, nutritional status, and quality of life, as well as the effect of these variables on surgical complications.

**Results:**

This study was funded in 2020 by the Center for Industrial Technology Development. Recruitment began in September 2021 and is expected to be completed in September 2022. Data will be analyzed and the results will be disseminated in 2023.

**Conclusions:**

The results of this protocol study could help to reduce surgery complications in patients with colorectal cancer using the new treatment Micodigest. This study could also identify new features associated with colorectal surgery complications. In summary, this study trial could improve the management of colorectal cancer patients.

**Trial Registration:**

Clinical Trials.gov NCT04821258; https://clinicaltrials.gov/ct2/show/NCT04821258

**International Registered Report Identifier (IRRID):**

DERR1-10.2196/34292

## Introduction

Colorectal cancer (CRC) is one of the most common malignancies in western countries. In 2018, about half a million cases were diagnosed in Europe, and 250,000 of those affected died due to this disease [1]. Most of the CRCs diagnosed are candidates for surgical resection with curative intent. Cure rates after surgery vary from 92% to 67% depending on the tumor stage [2]. However, colorectal surgery is associated with some life-threatening complications. There are several risk factors associated with these postoperative complications: age, sex, comorbidities, surgery urgency, tumor location, type of surgical approach, and surgical and hospital volume. Postoperative complications are detected during admission in 30% to 40% of patients who have had colorectal surgery [3-6]. Further, one study reported a lower percentage in the month after discharge (15%) and in the first year after surgery (25%) than at other times [3]. The most common complications are anastomotic failure, intra-abdominal infection, prolonged ileus, surgical site infection, deep vein thrombosis, pulmonary complications, and cardiac complications [6]. To assess the severity of surgical complications, different scales are available but the Clavien-Dindo classification is the most used in all parts of the world [7].

Some interventions have been proposed to reduce complications associated with colorectal surgery. Preoperative intravenous antibiotic prophylaxis is commonly used for the prevention of infectious postoperative complications [8]. The most appropriate regimen for antimicrobial prophylaxis for colorectal procedures and the optimal choice of antimicrobial agent have not been fully resolved. However, the last consensus international guidelines on antimicrobial prophylaxis recommend agents with activity against the anaerobic and aerobic floras of the bowel administered within 60 minutes before surgical incision [9]. Studies have shown that oral antibiotic administration can also reduce the risk of infections associated with surgery [10,11]. Other studies, however, have shown that this type of intervention does not modify the mortality and severity of other complications detected [12,13].

In studies analyzing the effect of probiotics, prebiotics, and symbiotics taken prior to the admission on surgery complications, results show that the use of prebiotics reduces the risk of infections associated with surgery and length of stay without affecting other surgery complications or mortality [14]. In addition, in a meta-analysis of 34 randomized clinical trials evaluating the role of probiotics or symbiotics in surgery complications, administration reduced infectious complications during admission without effect on mortality or noninfectious complications [15].

Human intestinal microbiota is a complex ecosystem that maintains homeostasis with the intestine and plays an essential role in wound healing and immune modulation [16,17]. Consequently, microbiota alterations resulting from surgical stress and perioperative management may be associated with the presence of postoperative complications [18]. Mechanical bowel preparation and antibiotic prophylaxis for colorectal surgery have a great impact on the diversity and composition of gut microbiota. It is known that mechanical preparation can both reduce the level of nonpathogenic bacteria like *Bifidobacterium* and *Lactobacillus* and increase pathogenic bacteria like *Escherichia coli* and *Staphylococcus* [19]. Similarly, antibiotic prophylaxis and surgical stress can also impact the gut microbiota by causing changes in diversity and relative abundance [19,20]. Recent studies using animal models have shown substantial alterations in the composition of intestinal microbiota after colon resection [21]. Kong et al [22] evaluated the changes in gut microbiota using fecal samples from 43 CRC patients collected before and after surgery. After CRC surgery, the Bacteroidetes/Firmicutes ratio and the number of obligate anaerobes (including *Bacteroides*, *Bifidobacterium*, *Faecalibacterium*, *Parabacteroides*, and *Prevotella*) decreased [23]. Further, tumor-associated bacteria were eliminated, and butyrate-producing bacteria (*Bacillus*, *Bilophila*, *Barnesiella*) were reduced [23]. On the contrary, conditionally pathogenic bacteria like *Escherichia*, *Shigella*, Enterobacteriaceae, and *Streptococcus* increased [23]. Therefore, alterations of gut microbiota could promote adverse outcome in CRC patients after surgery.

Fungal polysaccharides have attracted attention because of their role in gut microbiota modulation. This type of polysaccharide could reduce pathogen levels and stimulate the growth of beneficial microorganism [24]. As an example, some Basidiomycetes like *Ganoderma lucidum*, *Pleurotus eryngii*, or *Hericium erinaceus* have shown prebiotic activity in animal models [25-27]. In vitro and in vivo studies have shown that polysaccharides from fungi can regulate the microbiota through the fermentation of polysaccharides into short-chain fatty acids [24]. Human studies have also shown a stability for polysaccharides of more than 90% and a capability for stimulating *Lactobacillus* greater than the capability described for other prebiotics [28]. The beneficial effects of fungal polysaccharides is also shown in a randomized study comparing a diet for 10 days based on *Agaricus bisporus* or animal protein. Patients receiving a diet based on fungi showed more Bacteroidetes and fewer Firmicutes [29].

In addition to the beneficial effects of prebiotic activity, fungal polysaccharides have also shown anti-inflammatory activity [27,30]. Polysaccharides isolated from *Ganoderma* and *Lentinula edodes* have shown +immunomodulatory activity in colitis animal models through the production of nitric oxide, tumor necrosis factor alpha (TNF-α), and interleukin-6 (IL-6) [24]. Other examples are the effects of Basidiomycetes extract on the immunological function of inflammatory bowel disease patients and the ability of *G lucidum* to reduce the levels of pro-inflammatory cytokines in CRC patients [31,32]. In addition, some studies show that a combination of different fungal extracts is necessary to maximize the immunological function of different Basidiomycetes [33,34]. Hence, it seems that this combination could send multiple stimuli to the immune system, increasing intracellular reactions and interactions [35-37].

Micodigest 2.0 (Hifas da Terra) is a nutraceutical, available since 2016, that has had no adverse effects reported. Micodigest 2.0 was designed as a nutritional supplement for cancer patients. It is sold directly to the consumer for approximately 300€ (US $325.88) without a prescription from a health care professional. Micodigest 2.0 comprises 9 fungal extracts: *G lucidum*, *A blazei*, *Grifola frondosa*, *H erinaceus*, *Cordyceps sinensis*, *Inonotus obliquus*, *P ostreatus*, and *Polyporus umbellatus*. Taking into account the beneficial effects of fungal polysaccharides, we hypothesized that the fungal extract nutraceutical Micodigest 2.0 could be used to reduce complications after CRC surgery with curative intent.

For these reasons, we have designed a double-blind randomized clinical trial to evaluate the effect of Micodigest 2.0 on complications after surgery with curative intent for CRC. Apart from this purpose, we have also set the following secondary objectives:

Evaluate the safety of Micodigest 2.0 in CRC patientsEvaluate the effect of Micodigest 2.0 on fecal microbiome composition and diversityEvaluate the effect of Micodigest 2.0 on inflammatory pattern, nutrition status, and quality of lifeAnalyze the effect of the microbiome, inflammatory pattern, and nutrition status on complications after surgery

## Methods

### Study Design

We designed this study as a randomized, double-blind clinical trial. The study will be conducted in the gastroenterology department of Hospital Universitario de Ourense, Ourense, Spain. CRC candidates for surgery with curative intent will be considered for inclusion in the study. Patients who meet the criteria will be screened and randomly allocated to be treated with Micodigest 2.0 or placebo previous to admission. Additionally, we will stratify the included patients based on tumor location (distal or proximal to splenic flexure). The protocol includes a follow-up period of 4 to 6 weeks before surgery. This study has been developed in line with Standard Protocol Items: Recommendations for Interventional Trials (SPIRIT) guidelines [38].

### Ethics Approval and Consent to Participate

The study has been designed according to the Declaration of Helsinki and the latest Good Clinical Practice guidelines. Ethical approval was obtained from the clinical research ethics committee of Galicia, Spain (2021/ 036), and the study was registered at ClinicalTrials.gov [NCT04821258].

Informed consent will be obtained from all study participants. Any possible protocol modification will be communicated to the ethical committee and all relevant parties. The staff study members will inform participants that they can withdraw their consent to participate at any time and for any reason. Additionally, all study patients will receive an information sheet that will include objectives; methodology; interventions; action to be taken in case of forgetting treatment dose; benefits, risks, and possible adverse events; voluntary participation and right to withdraw; confidentiality; action to be taken with the remaining treatment at the end of the study; and information about the principal investigator. A trained medical doctor will provide these documents at the first visit.

### Inclusion Criteria

CRC patients will be aged 18 to 85 years, be a candidate for surgical treatment with curative intent (stage I-III), have an American Society of Anesthesiologists physical status classification of I or II and a score between 0 and 2 on the Eastern Cooperative Oncology Group scale, understand the information and make decision themselves (with preserved cognitive function), and provide authorization after reading the study information sheet.

### Exclusion Criteria

Patients who are candidates for neoadjuvant therapy, have concomitant carcinoma (carcinoma diagnosed in a person who has previously experienced another cancer at any time), are allergic to the supplied nutraceutical or previous medical diagnosis of malabsorption syndrome, have a mental disorder that can cause the loss of cognitive function, have active infection or have taken antibiotic therapy in the last month, or have had previous colectomy surgery will be excluded from the study.

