### Intervention

Patients will be randomized into 2 treatment groups: arm A (control) patients will be treated with placebo before surgery in the same way and timing as the nutraceutical and arm B (experimental) patients will be treated with Micodigest 2.0 before surgery.

The Hifas da Terra company will provide Micodigest 2.0 as 30 capsules and 300 mL syrup with a syringe to measure doses. The drinkable syrup consists of organic extracts from *G lucidum*, *A blazei*, *G frondosa*, *H erinaceus*, *Pleutorus eryngii*, *P ostreatus*, *Myrciaria dubia*, and purified water, raw agave, and natural aroma. The clear vegetable capsules contain *Levilactobacillus brevis*, *Lactiplantibacillus plantarum*, magnesium stearate, silicon dioxide, and extract from *G lucidum*. This treatment is a dietary supplement that has been available since 2016; no adverse effects have been reported. The treatment dose will initiate with 10 mL/day and 1 capsule/day (before breakfast or before lunch) for 7 days and increase to 20 mL/day and 2 capsules/day (10 mL + 1 capsule before breakfast and 10 mL + 1 capsule before dinner) until surgery admission (4-6 weeks).

In the same way, the Hifas da Terra company will supply placebo as 30 capsules and 300 mL syrup with a syringe to measure doses. The drinkable syrup consists of purified water, natural aroma, and agave nectar. This syrup also includes peptin and guar gums as gelling agents and potassium sorbate as preservative. The capsules contain hydroxypropyl methylcellulose and silicon dioxide as anticaking agents and microcrystalline cellulose as a gelling agent. The treatment dose will initiate with 10 mL/day and 1 capsule/day (before breakfast or before lunch) for 7 days and increase to 20 mL/day and 2 capsules/day (10 mL + 1 capsule before breakfast and 10 mL + 1 capsule before dinner) until surgery admission (4-6 weeks).

The assigned study intervention will end if allergic reactions or any serious adverse events are reported. Additionally, patient withdrawal will be a criteria for discontinuing any intervention.

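### The allergy exclusion covers the active product only, although the placebo lists at least four ingredients the active product does not, and the article gives two incompatible compositions for the active product

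*Protocol article*

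**What the plan says.** The only eligibility criterion in the protocol article that mentions allergy is in Exclusion Criteria. It excludes patients who "are allergic to the supplied nutraceutical or previous medical diagnosis of malabsorption syndrome".

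The Introduction fixes what the term means: "Micodigest 2.0 (Hifas da Terra) is a nutraceutical, available since 2016". The Intervention section keeps the two products apart, since control "patients will be treated with placebo before surgery in the same way and timing as the nutraceutical". The Randomization section allocates 1:1.

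The composition of the active product is given twice. The Introduction says "Micodigest 2.0 comprises 9 fungal extracts" and then lists them by name. The Intervention section gives a list by dosage form, beginning "The drinkable syrup consists of organic extracts from", followed by the capsule contents. The same section lists the placebo syrup and capsules; of the syrup it says "This syrup also includes peptin and guar gums as gelling agents and potassium sorbate as preservative".

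Allergy appears once more as a ground for ending treatment: "The assigned study intervention will end if allergic reactions or any serious adverse events are reported".

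**The concern.** An allergy exclusion is there to stop a patient with a known allergy from being given the substance. In a blinded placebo-controlled trial nobody knows at screening which kit a patient will get, so the criterion has to cover both kits. Here it names one. That would not matter if the placebo were the active product with the active ingredients left out, but its listed ingredients include gelling agents and a preservative that are not listed for the active product.

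A patient who has never taken the product can in practice be screened only against its ingredients, so the list matters. The article gives two that do not agree. The disagreement also has a consequence of its own, apart from allergy: it leaves unclear which mixture the trial is evaluating.

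**Working it through.** No sample-size or power formula applies. The check is a comparison of the lists.

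**1. Fungal composition of the active product**

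- Introduction: 9 extracts stated. Species named: *G lucidum*, *A blazei*, *G frondosa*, *H erinaceus*, *C sinensis*, *I obliquus*, *P ostreatus*, *P umbellatus*. Count = 8, so the stated 9 is not reproduced by the list that follows it.
- Intervention, syrup and capsules together: *G lucidum* (in both forms), *A blazei*, *G frondosa*, *H erinaceus*, *P eryngii* (genus misspelled in the article), *P ostreatus*. Count = 6. *Myrciaria dubia* is also in the syrup but is a plant and is not counted.
- In both lists: *G lucidum*, *A blazei*, *G frondosa*, *H erinaceus*, *P ostreatus* = 5.
- Introduction only: *C sinensis*, *I obliquus*, *P umbellatus*; 8 − 5 = 3.
- Intervention only: *P eryngii*; 6 − 5 = 1.
- Either list: 5 + 3 + 1 = 9.

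The stated 9 equals the number of species in the two lists combined, but not the number in either list.

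Counting extracts instead of species, with *G lucidum* counted once for each dosage form, the Intervention section gives 6 + 1 = 7 and the Introduction's names would give 8 + 1 = 9. This could rescue the count of 9 in the Introduction. It does not bring the two sections into agreement, because three species are still missing from one and one from the other.

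**2. Placebo ingredients against the active product (both from Intervention)**

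| Placebo ingredient | Listed for active product? |
|---|---|
| Purified water | Yes |
| Natural aroma | Yes |
| Agave (nectar; raw agave in active) | Yes, treated as the same |
| Silicon dioxide | Yes |
| Peptin (as printed) | No |
| Guar gums | No |
| Potassium sorbate | No |
| Microcrystalline cellulose | No |
| Hydroxypropyl methylcellulose | No, but uncertain |

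Nine placebo ingredients are listed and 4 are shared, so 9 − 4 = 5 are not listed for the active product. The active capsules are described only as vegetable, with no shell material stated, so hydroxypropyl methylcellulose could be present in them. Setting it aside leaves 5 − 1 = 4.

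**3. What the criterion does for such a patient**

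- Known allergy to, say, guar gum: not an allergy to the nutraceutical as listed, so the exclusion is not met. No other inclusion or exclusion criterion mentions allergy.
- Allocation 1:1: probability 1/2 of receiving the ingredient. If k such patients were randomised, k/2 would be expected to be exposed. The article gives no figure from which k could be estimated.
- The rule ending treatment requires a reported reaction, so it works after exposure and does not replace screening.

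**The case against.** The case on the other side has several parts.

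**An article condenses.** The exclusion is one sentence in a journal article, and wording at the level of components may sit in the full protocol or the screening form. The article's product terms are also loose: the Randomization section speaks of one dietary supplement being assigned to test or placebo. This has some weight, but the article does not merely leave the scope open. It ties the criterion to the nutraceutical, and the Intervention section contrasts that word with placebo. The narrow reading is the natural one.

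**Other safeguards exist.** A trained doctor gives each patient an information sheet covering interventions and risks, and weekly calls ask about adverse effects. These reduce the practical gap but do not exclude anyone.

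**The active arm is covered.** A reader might infer from the conflicting lists that the criterion cannot be applied to the active product at all. The documents do not support that. Allergy to the product is excluded whatever it contains, and the Intervention section, not the background in the Introduction, is the operative description of what will be supplied. The contradiction makes the scope ambiguous; it does not remove the rule. This objection stands.

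**Not listed is not the same as absent.** A reader might count five ingredients as exclusive to placebo. Because the active capsule shell is unspecified, five is an upper bound on what the lists show. This also stands, and the remaining four are enough for the point.

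**Conclusion.** The point holds as a minor safety and consistency correction, in two separate parts.

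First, the allergy exclusion as written does not cover at least four listed placebo ingredients, and an affected patient who is otherwise eligible could be randomised with a one-half chance of receiving one of them. This assumes that the Intervention lists are complete and that nutraceutical means Micodigest 2.0, as the article uses it.

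Second, the Introduction and the Intervention section disagree on the fungal composition in four species (3 + 1), and the stated count of 9 does not match the names that follow it. Which composition is correct cannot be told from the article.

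A reader might go further and infer that uncovered placebo allergies would add adverse events and discontinuations to the control arm, and so make the active product look safer in the planned comparison of adverse events. That would be the direction of any effect, but the documents give nothing to size it. The 72 of 144 patients planned for placebo are recipients, not patients at risk; the number with a relevant known allergy is not given and is probably small. The effect on any comparison is probably negligible, no material effect on the surgical-complication analysis is claimed, and no sample-size or power figure changes.

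**What to change.** - Reword the exclusion so that it covers known allergy to any ingredient of the active or placebo syrup or capsules, and check it at visit 0, where the selection criteria are already reviewed, against one combined ingredient list. The same list serves every patient, so blinding is unaffected.
- For that list, state the shell material of the active capsules and correct the spelling of the ingredients.
- Reconcile the compositions in the Introduction and the Intervention section with the product actually supplied, correct the count of 9 or explain how extracts are counted, and account for *C sinensis*, *I obliquus*, *P umbellatus* and *P eryngii*.

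The cost is a change of wording, one combined list and at most a few more exclusions. The sample size and the analysis stay as they are.

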### Randomization

We will randomize into the 2 parallel treatment arms using the distribution of a blinded treatment kit containing test or placebo supplementation. We will perform randomization using a code list randomly created using R software (R Foundation for Statistical Computing). This code list will include a total of 144 random numbers. Each random number will match with a unique identification code that will identify test or placebo. The randomization will ensure an equal sample size for each group. The dietary supplement will be randomly assigned into the test or placebo groups at a 1:1 ratio according to the random numbers generated.

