### Outcomes and Data Collection

#### Medical History

Data regarding inclusion and exclusion criteria, demographic variables, tumor location, tumor stage, and type and duration of symptoms will be collected at first visit. At the time of patient discharge, we will also recover data about type of surgery, length of stay, vital status, type of surgery complications, and stratification of postoperative complications according to the 5 categories in the Clavien-Dindo classification.

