#### Fecal Samples

Fecal samples will be collect at baseline and closeout visits. Patient will collect the samples at home and deliver them to the clinic within 4 hours of collection. Again, samples will be frozen at –20 ℃ until analysis. Fecal sample analysis will start with a high-quality DNA extraction. The analysis will continue with the bacterial 16S ribosomal RNA gene being sequenced on a MiSeq benchtop sequencer (Illumina Inc). Finally, microbiome composition will be defined using metagenomic species and a database with >200,000 strains.

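### Baseline stool is screened for recent antibiotics but not recent bowel preparation, and the paired McNemar test lets recovery shared by both arms look like a change on the product

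*Protocol article*

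**What the plan says.** The Introduction states: "Mechanical bowel preparation and antibiotic prophylaxis for colorectal surgery have a great impact on the diversity and composition of gut microbiota". It adds that preparation lowers *Bifidobacterium* and *Lactobacillus* and raises *Escherichia coli* and *Staphylococcus*.

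The Exclusion Criteria rule out patients who "have active infection or have taken antibiotic therapy in the last month". The list closes with "or have had previous colectomy surgery will be excluded from the study" and has no item on bowel preparation. Under Medical History, "demographic variables, tumor location, tumor stage, and type and duration of symptoms will be collected at first visit"; neither there nor in the Study Period section (Table 1 and the visit descriptions) does a date of last preparation appear.

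On sampling, "Fecal samples will be collect at baseline and closeout visits", and the two visits lie 4 to 6 weeks apart (Study Design: "The protocol includes a follow-up period of 4 to 6 weeks before surgery").

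For the microbiome, Inferential Statistics states a between-group aim but names McNemar tests together with t tests. It then relates the microbiome to complications by univariate and multivariate regression, without saying which time point is used.

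**The concern.** The authors identify two disturbances of the microbiota, and their entry rule deals with one. Participants are newly diagnosed colorectal cancer patients who have just passed the tumor board, so a recent diagnostic colonoscopy with preparation is plausible for many. If so, baseline values partly reflect how long ago that preparation was, and part of the change to closeout is recovery.

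That recovery would resemble the effect hoped for. The active capsules contain two lactobacilli (Intervention), and the Introduction expects fungal polysaccharides to stimulate *Lactobacillus*. A rise in *Lactobacillus* from baseline to closeout is what a working product would produce, and also what plain recovery would produce.

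At stake is the reading of a secondary endpoint and of any complication model that takes in baseline microbiome values.

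**Working it through.** The plan gives no figure for the microbiome endpoint, so there is none to reproduce. The only number borrowed from the protocol is 64 patients per arm (Sample Size, before the dropout allowance). Drift sizes, noise sizes and correlations below are assumptions.

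**1. What McNemar can compare.** The test needs paired binary data. The two arms are independent groups, so in this design the natural pairing is baseline with closeout in the same patient. The named test therefore answers a within-patient question, while the stated aim is a difference between arms.

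**2. Within-arm test with no product effect.** Suppose recovery shifts the mean by d SD. A paired t test stands in for the within-arm comparison, with n=64, r=0.5 and two-sided .05.
- SD of change = √(2(1−r)) = √(2×0.5) = 1 SD.
- Noncentrality = d×√64 = 8d, that is 1.6, 2.4 and 3.2 for d = 0.2, 0.3 and 0.4.

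| Average drift d | Significant within active arm | Significant in active arm only, p(1−p) |
|---|---|---|
| 0 | 5% | 0.05×0.95 = 5% |
| 0.2 SD | 35.1% | 0.351×0.649 = 23% |
| 0.3 SD | 65.7% | 0.657×0.343 = 23% |
| 0.4 SD | 88.3% | 0.883×0.117 = 10% |

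A simulation of 20,000 trials gave 35% and 66% at 0.2 and 0.3 SD, with the active-only pattern in 22% to 23%. If only half the patients are disturbed, by 0.5 or 0.8 SD (averages 0.25 and 0.4), the within-arm test is significant in 48% and 83%.

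**3. Between-arm test with no product effect.** In the same simulation, a t test comparing change between arms was significant in about 5% of trials at every drift from 0 to 0.8 SD, and also when half the patients were disturbed. The drift cancels because both arms share it.

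**4. Precision, only if baseline is used.** Let a clean baseline correlate 0.6 with closeout, and let varying time since preparation add independent noise of s = 0.5 to 1.0 SD. Closeout variance is 1.
- Correlation = 0.6/√(1+s²) = 0.54 and 0.42.
- Residual variance after baseline adjustment = 1−r²: 0.64 with a clean baseline, 0.71 (s=0.5) and 0.82 (s=1.0), a rise of 11% and 28%.
- Change-score variance = 2(1−0.6)+s²: 0.80 with a clean baseline, then 1.05 and 1.80.

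On these figures baseline adjustment still beats an unadjusted closeout comparison (variance 1), whereas change scores become worse than it.

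**The case against.** The strongest answer is the design itself. Control "patients will be treated with placebo before surgery in the same way and timing as the nutraceutical", and "The dietary supplement will be randomly assigned into the test or placebo groups at a 1:1 ratio according to the random numbers generated". Both arms recover alike, so a rise also seen on placebo is no evidence for the product, and the stated aim is a between-group difference. This stands: a reader might infer that the randomized microbiome comparison is biased, and it is not. What remains is that the named paired test does not deliver that aim. A significant active arm beside a non-significant placebo arm is easy to misread, even with a control group present.

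It can be said that this is a fault of test choice, not of eligibility. Largely so, and the first part of the fix addresses the test. The preparation date still matters wherever baseline values enter an analysis.

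The documents mention no diagnostic colonoscopy, no interval before visit 1 and no recovery time, and the Introduction speaks of preparation for surgery. Nor do they say why the antibiotic criterion exists. All this stands. Drift may be zero if the stool has recovered by visit 1, and then the within-arm error is the usual 5%.

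The 35% to 88% belongs to a paired t test on a continuous measure. McNemar on a dichotomized measure would give other figures. The 11% to 28% loss applies only to baseline-adjusted analyses, and the change-score figures only to change scores; Inferential Statistics specifies neither. An unadjusted closeout comparison loses nothing.

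A condensed article need not list every data field, and visit 1 does record previous medical history. So the missing date is no error in itself, only a reason to confirm that it can be retrieved.

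**Conclusion.** The point holds at minor severity. The protocol names two disturbances of the microbiota, screens for one, and assigns to the microbiome question a paired test through which shared recovery can be mistaken for a product effect. The illustrative size is 35% to 88% of null trials for an average drift of 0.2 to 0.4 SD, and about 5% with no drift. It rests on the assumptions that many patients had a recent diagnostic preparation and that its effect lasts to visit 1 but fades by closeout.

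Two further inferences are not supported. The primary complication comparison is not affected. Nor do the documents give much ground for confounding of the complication model by surgical urgency. The Introduction lists urgency as a risk factor, but every participant is ASA I or II and planned for 4 to 6 weeks of preoperative treatment, so urgency can vary little. The protocol also does not say that baseline rather than closeout microbiome values enter that model.

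**What to change.** 1. In Inferential Statistics, replace the McNemar tests for the microbiome with a between-arm comparison at closeout, adjusted for the baseline value. State that product effects on the microbiome are claimed only from that contrast and never from a change within one arm. This costs a change of wording.
2. Take the date of the last bowel preparation from the hospital record, and include days since preparation as a covariate wherever baseline microbiome values are used, in the microbiome comparison or the complication model. This costs one date field and one covariate. It can be done retrospectively for patients already recruited, excludes nobody and adds no procedure.
3. Optionally, repeat the microbiome comparison without baseline stools taken within one month of preparation, the window the protocol already uses for antibiotics. This may leave few patients and should be labelled as a sensitivity analysis.
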